To address this gap, MedRhythms developed MR-001, an autonomous neurorehabilitation system that delivers individualized RAS in the home. A pilot study with an early prototype of MR-001 demonstrated that a fully automated, music-based RAS session reduced walking energy cost by ~9% and improved gait asymmetries by over 20% in individuals with chronic hemiparesis [35]. In a recent randomized controlled trial (RCT) [36] of 87 individuals with chronic post-stroke gait impairment (average >8 years post-stroke), participants who used MR-001 three times per week for 5 weeks improved walking speed by 22%, more than double the gain seen in controls (*p* = 0.013). Notably, 40% of MR-001 users exceeded the minimal clinically important difference (MCID) of 0.16 m/s [37]. They were also 3.7 times more likely to achieve both the MCID threshold and the community ambulation threshold of ≥0.8 m/s (*p* = 0.011). These findings demonstrate that stroke survivors many years after their initial event are still capable of achieving clinically meaningful gains with MR-001. Moreover, improvements continued to accrue over the 5-week intervention without evidence of plateau, supporting the potential for continued benefit with ongoing use.

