### Objectives {7}

This study aims to evaluate user patterns of engagement, clinical effectiveness, durability of response, and health economic impact on participants post-stroke who complete the MR-001 intervention in the home setting. The primary objective is to assess engagement with the MR-001 neurorehabilitation system, measured by the proportion of participants achieving at least moderate engagement over the 12-week intervention period. The secondary objectives are to evaluate: (1) the effects of MR-001 on walking endurance, as measured by the 6-Minute Walk Test (6MWT); (2) the durability of this effect following 12 weeks of intervention; and (3) the effects of MR-001 on health-related quality of life, activities of daily living, social isolation, and cognition and executive function. Exploratory objectives include assessing: (1) changes in general mobility, as measured by the Timed Up and Go Test (TUG); (2) the effects of a second period of treatment on walking endurance and general mobility following a 3-month no-intervention period; (3) the differential intervention effects across subgroups (e.g., engagement and baseline gait impairment subgroups); (4) the proportion and predictors of responders; and (5) healthcare resource utilization, assessed through claims data analysis.

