### Trial design {8}

This longitudinal, pragmatic, decentralized hybrid trial integrates home-based implementation of the MR-001 therapy with selected controlled trial elements to maximize external validity while maintaining scientific rigor. In this study, “home-based” refers to any environment outside of a professional healthcare facility consistent with the FDA definition [39]. A two-step, withdrawal with randomized re-treatment (delayed randomization) design allows assessment of treatment engagement, clinical outcomes, durability of benefit, and the effects of re-treatment in the home setting. This hybrid design allows for evaluation of both immediate and sustained effects of the intervention, as well as the potential benefit of reintroduction following initial use. Spanning ~52 weeks, the study follows a decentralized design without traditional clinical trial sites. In-person assessments are conducted at more than 30 designated physical assessment center locations across the USA, chosen to ensure broad geographic representation of the population.

Step 1: All participants receive 12 weeks of MR-001 intervention (30 min per session, three times per week), followed by a 12-week washout. The 12-week intervention period was selected based on (1) extending the established evidence that users do not plateau after 5 weeks of MR-001 intervention [36] and (2) stroke rehabilitation evidence supporting this duration as effective for achieving clinically meaningful gains in walking capacity [40]. This timeframe also aligns with guidelines recommending sustained, task-specific therapy to support neuroplasticity and motor learning [14], and reflects typical US outpatient rehabilitation reimbursement models, which frequently authorizes approximately 36 therapy sessions over 12 weeks [41]. Participants self-administer MR-001 in their home environment, with remote support provided by the study team throughout the 12-week intervention period.

Step 2: At the end of the washout, participants are randomized 1:1 to either receive the MR-001 intervention for another 12 weeks followed by 12 weeks of washout, or continue with an additional 24-week washout. Participants and investigators are unblinded to the Step 2 allocation, but in-person assessors remain blinded.

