### Participant timeline {13}

After providing informed consent, participants complete screening assessments within 28 days prior to baseline, including demographic and medical history (with past falls), eligibility confirmation, and in-person testing with the 6MWT, TUG, and TMT A and B.

Baseline assessments are conducted within 14 days before starting the intervention and include the PHQ-8, PROMIS Social Isolation Scale, BI, and falls/adverse event documentation. Participants then complete a 12-week intervention phase with three MR-001 walking sessions per week, supported by engagement calls. Primary and secondary outcomes are reassessed at the end of week 12. Follow-up visits at weeks 16 and 24 evaluate maintenance of effects during the washout period.

Randomization occurs at the end of week 24, assigning participants to either cohort A, which receives the MR-001 intervention for another 12 weeks (weeks 25–36), or cohort B, which continues washout. Outcome assessments are repeated at weeks 36 and 48. Claims re-authorization is performed, as needed, and healthcare utilization data are collected throughout the study with a final follow-up call conducted at approximately week 60 to ensure collection of 52 weeks of HCRU data. The participant timeline detailing the schedule of enrollment, interventions, and assessments is illustrated in Table 1.

**Table 1 Tab1:** Participant timeline

	Step 1						Step 2			
	Screening	Baseline (T1)	Intervention Step 1	Post- Intervention (T2)	Follow Up 1 (T3)	Follow-Up 2 (T4)	Intervention Step 2/Cont. Washout	Follow-Up 3 (T5)	Follow-Up 4 (T6)	Follow-Up call (as needed)
**Timepoint**	Day −28 to day 0	Day −14 to Day 0	Weeks 1–12	End of week 12 (+/- 7 days)	End of week 16 (+/- 7 days)	End of week 24 (+/- 7 days)	Weeks 25 - 36	End of week 36 (+ 14 days)	End of week 48 (+ 28 days)	Through Week 60

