## Assignment of interventions: allocation

### Sequence generation {16a}

Randomization for Step 2 is performed using Python’s built-in random shuffle function. Participants are randomized in a 1:1 ratio to either receive another 12 weeks of MR-001 intervention (cohort A) or continue washout for an additional 24 weeks (cohort B).

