### Methods for additional analyses (e.g., subgroup analyses) {20b}

#### Exploratory analyses

Exploratory analyses are planned to provide additional insight into the effects of MR-001 and to identify factors that may influence treatment response. These will include:

Change in general mobility (TUG): Mobility will be assessed at multiple study visits across the intervention, follow-up, and re-treatment phases. Analyses will explore whether the MR-001 intervention is associated with sustained or progressive improvements in functional mobility, as well as whether gains are maintained after withdrawal or re-established with re-treatment.Clinical responsiveness: Participants who achieve at least the minimal clinically important difference (MCID) on the 6MWT will be classified as responders. This analysis will help quantify the proportion of patients experiencing a clinically meaningful benefit, complementing the mean change analysis.Predictors of response: Baseline demographic and clinical characteristics, as well as engagement levels with the device, will be examined as potential predictors of responder versus non-responder status. This analysis is intended to inform which subgroups may benefit most from the intervention.Durability of re-treatment: Among participants who undergo a second round of intervention following the withdrawal phase, changes in walking mobility and endurance will be compared before and after re-treatment to assess whether the intervention effect can be re-established.

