### Methods in analysis to handle protocol non-adherence and any statistical methods to handle missing data {20c}

Primary analysis will follow an intention-to-treat (ITT) approach, including all randomized participants in their assigned groups (for Step 2) regardless of adherence or protocol deviations. A per-protocol (PP) analysis will also be performed, excluding participants with major protocol violations.

Missing data will be handled under the missing at random (MAR) assumption. For the primary endpoint, participants who initiate the intervention but discontinue before completion will be classified as non-engaged. For secondary and exploratory outcomes, longitudinal analyses will use linear mixed models (LMM), which inherently accommodate incomplete follow-up data without the need for additional imputation by maximum likelihood estimation. This approach includes all available observations while appropriately addressing missingness conditional on observed data.

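### The only re-treatment analysis the article spells out is a before/after change among those who take the second course; it leaves out the concurrent randomised cohort B

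*Protocol article*

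**What the plan says.** The exploratory objective in Objectives {7} is to assess "the effects of a second period of treatment on walking endurance and general mobility following a 3-month no-intervention period".

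The design provides a concurrent control for it. Under Trial design {8}, "participants are randomized 1:1 to either receive the MR-001 intervention for another 12 weeks followed by 12 weeks of washout", the alternative being a further 24 weeks of washout. Sequence generation {16a} repeats the allocation: "Participants are randomized in a 1:1 ratio to either receive another 12 weeks of MR-001 intervention (cohort A) or continue washout". Under Participant timeline {13}, "Outcome assessments are repeated at weeks 36 and 48", and Table 1 marks 6MWT and TUG at both visits without limiting them to one cohort.

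The analysis is under Exploratory analyses, in the item on durability of re-treatment. Its population is "Among participants who undergo a second round of intervention following the withdrawal phase", and its contrast is that "changes in walking mobility and endurance will be compared before and after re-treatment to assess whether the intervention effect can be re-established".

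Section {20c} describes an intention-to-treat approach "including all randomized participants in their assigned groups (for Step 2) regardless of adherence or protocol deviations".

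No section writes out a cohort A versus cohort B comparison. Outcomes {12} lists the Step 2 6MWT results with no contrast, and the TUG item under Exploratory analyses names no comparator for re-treatment.

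**The concern.** Step 2 is the only randomised part of the trial, and the trial's title rests on it. The question is what a second course does. A before/after change in those who took it answers a different one: how far these people moved between week 24 and the later visits, for whatever reason.

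That movement mixes any device effect with underlying time trend, repeat testing and the physical and occupational therapy allowed under {11d}. Restricting the analysis to people who undergo the course can also select the more able or more motivated, if some allocated to cohort A never start. Cohort B is followed over the same weeks with the same tests and would carry the shared part of these influences, but the stated analysis leaves it out.

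A reported re-treatment effect could then be partly or wholly drift. If untreated walking declines, a real effect could be understated. The Discussion says the results will help inform intermittent or repeated use, so the contrast matters even though it is exploratory.

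**Working it through.** **1. The plan's own figures.** The article gives no sample size, power, test or SD for any Step 2 comparison, so there is no Step 2 figure to reproduce. The one stated power, 98% for engagement (60% null, 72% true, one-sided 0.05), reproduces as 0.983 by exact binomial at N = 225. It does not bear on this point.

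**2. The texts side by side.**
- Design: two randomised cohorts, same tests, same weeks (Trial design {8}, Table 1).
- Objective: the effect of a second treatment period.
- Stated analysis: one group, defined by having undergone treatment, compared with itself.
- Section {20c}: all randomised participants, in assigned groups, whatever their adherence.

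The third line cannot be carried out under the fourth, and it does not use the first.

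**3. Inputs for an illustration.**
- Completers: 225 × (1 − 0.20) = 180 (Sample size {14}); at 1:1, 180 / 2 = 90 per cohort.
- SD of the 6MWT change from week 24 to week 36: not in the article. Assumed 45 m, range 35 to 55 m.
- Gain not due to the device: unknown. Assumed 5, 10 or 15 m.
- Two-sided 5% t-tests, counting only significant results in the positive direction. This test is my assumption; the article specifies none.

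**4. Before/after test in cohort A, true device effect zero.** Standard error = SD / √n = 45 / √90 = 4.74 m. For a 10 m gain the standardised shift is 10 / 4.74 = 2.11.

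| Non-device gain | Shift | Declared a re-treatment gain |
|---|---|---|
| 0 m | 0 | 2.5% |
| 5 m | 1.05 | 18% |
| 10 m | 2.11 | 55% |
| 15 m | 3.16 | 88% |

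For the 10 m gain, an SD of 35 m gives about 77% and an SD of 55 m about 40%.

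**5. Cohort A minus cohort B.** A gain common to both cohorts cancels, so the upper-tail error stays at 2.5% whatever that gain is. Standard error = SD × √(2/n) = 45 × √(2/90) = 6.71 m. Power at SD 45 m is 32% for a 10 m difference, about 60% for 15 m, 84% for 20 m (20 / 6.71 = 2.98) and 96% for 25 m.

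**6. The opposite direction.** If the device adds 20 m while walking without it drifts by −10 m, the expected before/after change is 20 − 10 = 10 m. That is detected in about 55% of trials and reported at half its true size. The between-cohort contrast still targets 20 m, with 84% power.

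**7. Price in precision.** The ratio of the unadjusted standard errors is 6.71 / 4.74 = √2, about 1.4.

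**The case against.** The strongest reply is that the article does not say cohort B will go unused. Its list of exploratory analyses is not presented as exhaustive, Outcomes {12} lists Step 2 results without limiting them to cohort A, section {20c} keeps assigned groups for Step 2 and applies mixed models to exploratory outcomes, and analysts are blinded to assignment until database lock. These provisions suggest that a between-cohort comparison may be intended, perhaps in an analysis plan not shown. This stands in part: a reader might infer that the randomisation is discarded altogether, and the documents do not support that. What remains is that the one re-treatment contrast the article does fix is the weaker one.

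It can also be said that the intention-to-treat sentence opens with the primary analysis, and that undergoing a second round may simply mean belonging to cohort A. Both readings are possible. But the primary endpoint is single-arm Step 1 engagement, so the Step 2 clause then has no stated analysis to govern. Even with all of cohort A included, the contrast is still before/after.

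Three further limits stand.
- A reader might take the prior trial, in which device users "improved walking speed by 22%, more than double the gain seen in controls", to mean that up to nearly half of a before/after gain here would be non-device. That does not transfer. Its controls did unassisted walking, it lasted 5 weeks and the figure is for speed; cohort B has no assigned walking. By week 24 each participant has also been scheduled for four 6MWTs (screening, weeks 12, 16 and 24), so further retest gain may be small.
- Randomisation does not remove everything. Step 2 is open label, and the weekly emails and check-in calls go with having the device. Expectation, attention, differential drop-out and co-therapy begun after allocation can all remain in the between-cohort difference.
- A reader might fault the covariate list in {20a} for naming baseline speed rather than the week-24 value. That list belongs to the secondary analyses and is not stated for Step 2.

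**Conclusion.** The concern holds in a limited form. The only re-treatment analysis spelled out with both a population and a contrast is a within-person change among those who take the second course. It leaves out the concurrent randomised cohort and does not fit the assigned-group wording for Step 2. It therefore cannot isolate the effect named in the objective, and the error may run either way.

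The size is unknown. The 55% figure depends on an assumed 10 m non-device gain, an assumed SD of 45 m, 90 people in cohort A and a test the article does not specify; it shows what could happen and is not an estimate for this trial. With no drift, the before/after test keeps its nominal error.

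Severity is moderate. Re-treatment is exploratory throughout, with no stated power or decision rule, and the primary endpoint, the secondary endpoints and the sample size are untouched.

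**What to change.** Replace the re-treatment item with a statement along these lines: the exploratory re-treatment effect is the cohort A minus cohort B difference in 6MWT and in TUG at week 36 (end of the second course) and at week 48, in all randomised participants as assigned, estimated from the planned linear mixed model with a cohort-by-visit term and the week-24 value of the same test as the pre-randomisation baseline, and reported with a 95% confidence interval. Keep the change within cohort A as descriptive only, and name the same comparator in the TUG item. If the analysis plan already contains this contrast, bring the article's wording into line with it.

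The cost is a change of text; all the data are already scheduled for collection. The unadjusted interval is about 1.4 times as wide as the before/after one, and adjusting for week 24 should recover part of that. The report should say that, because Step 2 is open label, the difference still includes expectation and attention effects.

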#### Health economics analyses

In addition, the study will explore the impact of MR-001 on healthcare resource utilization (HRU) among participants. The feasibility of this analysis depends on (1) adequate long-term retention of participants, (2) successful linkage of participants to claims data, and (3) availability of funding. If all conditions are met, analyses will proceed as described below; otherwise, the HRU analysis will not be conducted (go/no-go criterion). Depending on data availability and funding resources, analyses could include an external control arm (ECA), matched to trial participants on key baseline characteristics, developed from electronic health records or claims databases, or deploy a within-subject design where HRU will be compared before and after MR-001 enrollment within participants, using appropriate longitudinal methods.

The planned economic analyses are subject to refinement to ensure alignment with available data and evolving methodological standards. A detailed Health Economics Analysis Plan (HEAP) will be finalized prior to analysis.

### Methods in analysis to handle protocol non-adherence and any statistical methods to handle missing data {20c}

Primary analysis will follow an intention-to-treat (ITT) approach, including all randomized participants in their assigned groups (for Step 2) regardless of adherence or protocol deviations. A per-protocol (PP) analysis will also be performed, excluding participants with major protocol violations.

Missing data will be handled under the missing at random (MAR) assumption. For the primary endpoint, participants who initiate the intervention but discontinue before completion will be classified as non-engaged. For secondary and exploratory outcomes, longitudinal analyses will use linear mixed models (LMM), which inherently accommodate incomplete follow-up data without the need for additional imputation by maximum likelihood estimation. This approach includes all available observations while appropriately addressing missingness conditional on observed data.

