**Methods:**

This decentralized, longitudinal trial combines a pragmatic single-arm intervention phase with a randomized re-treatment phase. Approximately 225 participants with chronic stroke and gait deficit will be enrolled. In Step 1, all participants receive 12 weeks of MR-001 therapy (30 min, 3 times per week) followed by a 12-week washout. In Step 2, participants are randomized to either 12 additional weeks of MR-001 or a 24-week extended washout. The primary endpoint is user engagement, defined as the proportion achieving at least moderate engagement during Step 1. Secondary endpoints include walking endurance, durability of gains, quality of life, activities of daily living, social isolation, and cognitive function. Exploratory analyses include changes to general mobility, effects of re-treatment, subgroup analyses by baseline function and engagement, proportion and predictors of responders, and healthcare resource utilization assessed through claims data.

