### Sample size {14}

The target enrollment is 225 participants, allowing for an anticipated 20% attrition to yield approximately 180 participants completing the study. The calculation is based on the primary endpoint of device engagement, tested using a one-sided binomial proportion test with alpha = 0.05 against a null hypothesis of 60% engagement. Assuming a true engagement rate of 72%, this sample size provides 98% power to reject the null. Exploratory analyses will also assess engagement thresholds of 70% and 80%.

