### Implementation {16c}

Eligible participants who complete Step 1 are randomized at the week 24 visit. The CTMS automatically assigns participants to their allocated cohort after completion of all required week 24 assessments. Site personnel communicate the assignment to participants and initiate the appropriate Step 2 procedures.

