## Statistical methods

### Statistical methods for primary and secondary outcomes {20a}

Primary analysis: The primary endpoint is engagement with MR-001, defined as the proportion of participants achieving at least moderate engagement. Engagement will be categorized as low, moderate, or high based on predefined thresholds of weeks, sessions, and minutes of use. The primary hypothesis is that the proportion of participants achieving at least moderate engagement exceeds a benchmark of 60%. Sensitivity analyses will be conducted at thresholds of 70% and 80%. A one-sided binomial proportion test will be used at significance level *α* = 0.05. Participants who initiate the intervention but withdraw from the study prior to completion of the planned intervention will be classified as non-engaged in the primary analysis.

Secondary analyses: Secondary endpoint analyses will evaluate mean changes from baseline to post-intervention for walking endurance (6MWT), depressive symptoms (PHQ-8), independence in activities of daily living (BI), social isolation (PROMIS Social Isolation Scale), and cognitive and executive function (TMT A and B).

Durability of walking endurance will be assessed at 16-week and 24-week follow-up visits after discontinuation of the intervention at 12 weeks. Results at these follow-up visits will be compared with the post-intervention assessment to determine whether the gains achieved during treatment are sustained. The analysis will be conducted using a non-inferiority framework, with a pre-specified margin of one-half of the minimal clinically important difference (17.2 m) [52]. This approach is designed to test whether the benefits observed during the intervention period are retained after device use is discontinued. Linear mixed modeling (LMM) will be used to estimate the changes over time. Random intercepts and/or modeling the covariance matrix of the error terms will be used to account for repeated measures. Model choices will be made based on minimizing Akaike Information Criteria (AIC) and Bayesian Information Criteria (BIC). Age, sex, baseline speed, and time since stroke will be evaluated and included as covariates if they are predictive of the change scores.

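### The stated intention-to-treat set does not fit the Step 1 engagement endpoint, and the non-engaged rule leaves never-starters unplaced and has two different triggers

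*Protocol article*

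**What the plan says.** The Abstract gives the primary endpoint as user engagement, "defined as the proportion achieving at least moderate engagement during Step 1". Outcomes {12} places it in the 12-week treatment phase, classified from device logs of weeks, sessions and minutes. Sample size {14} says it is "tested using a one-sided binomial proportion test with alpha = 0.05 against a null hypothesis of 60% engagement".

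Three passages bear on the denominator:

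- Section {20c}, on the analysis set: "Primary analysis will follow an intention-to-treat (ITT) approach, including all randomized participants in their assigned groups (for Step 2"), regardless of adherence or deviations.
- Implementation {16c}, on who is randomised: "Eligible participants who complete Step 1 are randomized at the week 24 visit".
- The non-engaged rule, stated twice. In {20a} it applies to "Participants who initiate the intervention but withdraw from the study prior to completion of the planned intervention". In {20c} it reads: "participants who initiate the intervention but discontinue before completion will be classified as non-engaged".

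The article names no other analysis set for the primary endpoint, apart from a per-protocol set that excludes major protocol violations.

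**The concern.** Engagement is a proportion tested against a fixed benchmark, so the choice of denominator largely decides the result. Three things are unsettled.

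1. **The set.** The sentence that begins with the primary analysis names a population formed 12 weeks after the primary endpoint window closes, and only from people who got through Step 1. Someone who stops in week 3 is never randomised, so that person cannot be both outside the set and counted in it as a failure.
2. **Never-starters.** Both versions of the rule begin with people who initiate. Recruitment {15} puts baseline planning, kit shipment and a setup call between the eligibility decision and the first session, so an enrolled participant with a kit and no sessions is possible. Neither version says where that person goes.
3. **The trigger.** Section {20a} requires withdrawal from the study; {20c} requires only discontinuation. Section {11b} allows a participant to withdraw from the intervention. If that person stays in the study, {20c} makes them non-engaged automatically and {20a} does not.

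The trial sets out to characterise real-world adherence, and people who stop early or never start are central to that question.

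**Working it through.** **Inputs.** From Sample size {14}: null rate 0.60, assumed true rate 0.72, one-sided alpha 0.05, 225 enrolled, 20% attrition, about 180 completing. From {16c} and the participant timeline {13}: randomisation at the end of week 24, among Step 1 completers. The document gives neither the number of never-starters nor the timing of attrition, so both are assumptions below.

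**Step 1: reproduce the plan's figure.** For sample size n, find the smallest r with P(X ≥ r | n, 0.60) ≤ 0.05. Power is then P(X ≥ r | n, 0.72).

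| n | r | r/n | exact alpha | power at 72% |
|---|---|---|---|---|
| 225 | 148 | 65.8% | 0.0435 | 98.3% |
| 180 | 120 | 66.7% | 0.0390 | 95.1% |

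The inflation is correct: 180/(1 − 0.20) = 225. The stated 98% agrees with n = 225 and not with n = 180, so the sample size section implies a denominator of everyone enrolled.

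**Step 2: the literal randomised-only reading, as an upper bound.** Assume that all 20% attrition falls before week 24 and that everyone lost is non-engaged. The set is then 180 and success needs 120 engaged participants. As a share of those enrolled this is 120/225 = 53.3%, below the 60% benchmark. With all enrolled, success needs 148/225 = 65.8%.

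**Step 3: never-starters alone.** Suppose that true engagement is exactly 60% of all enrolled, so the null holds, and that a share d never starts and is left out. The rate among those kept is 0.60/(1 − d). The chance of declaring success is P(X ≥ r | n, 0.60/(1 − d)), with n = 225(1 − d) and r found as in Step 1.

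| d (assumed) | n | r | rate among kept | chance of success, n fixed | chance of success, n varying |
|---|---|---|---|---|---|
| 2% | 220 | 145 | 61.2% | 8.7% | 8.7% |
| 5% | 214 | 141 | 63.2% | 22.5% | 22.3% |
| 10% | 202 | 134 | 66.7% | 57.2% | 59.7% |

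The last column lets the number left out vary at random (simulation). The nominal level is 5%, and the exact level with all 225 in the denominator is 4.35%.

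**Step 4: direction.** Leaving out a never-starter or a low-use early withdrawal can only raise the proportion. A randomised-only set would also lose people who engaged well in weeks 1 to 12 and left during the week 13 to 24 washout, and losing them lowers it. The net bias under the literal reading therefore depends on who leaves and when. For never-starters it is upward.

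**The case against.** The strongest reply is that the set sentence in {20c} carries the qualifier for Step 2 and speaks of assigned groups, which makes sense only after randomisation. On that reading it says nothing about Step 1. The non-engaged rule, stated twice and tied to the primary endpoint, then shows that starters who withdraw stay in the denominator, and the power figure supports this. The reply has force. A reader might infer that the plan drops its least engaged participants from the primary analysis; the text does not establish that. On the benign reading, however, the article states no Step 1 set at all, and a sentence introduced as the primary analysis still fails to describe the primary endpoint.

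A second reply is that never-starters are unmentioned rather than excluded, and that zero logged use would ordinarily fall in the low category. This also stands as far as it goes: they are unplaced. But a rule written explicitly for people who initiate invites the reading that the set consists of starters.

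Third, the 20% attrition covers the whole study of about 52 weeks, so 180 is not a forecast of the randomised number. That is correct, and the figure of 53.3% is only a bound. A reader might also discount the planned 72% for never-starters and conclude that power is lost. The document gives 72% as the true engagement rate without tying it to starters; applied to all enrolled, power remains 98.3%.

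Fourth, the difference in triggers is minor, because someone who stops the device but stays in the study has logs that the thresholds can classify. That limits its effect, but the two rules can still give different answers for the same person.

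Finally, formal analysis sets are commonly left to the statistical analysis plan. Here the article does state a set and a rule, and the two do not agree.

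**Conclusion.** The point holds as a conflict in the text. The intention-to-treat sentence in {20c} does not fit a single-arm weeks 1 to 12 endpoint and, read literally, contradicts the non-engaged rule in {20a} and {20c}. The rule leaves never-starters without a stated place and has two triggers. Only never-starters are at risk of omission on either reading; starters who withdraw are lost only on the literal one.

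The possible size ranges from small to decisive. With an assumed 2% of never-starters left out, the false-success chance is about 9%; with 5% it is about 22%, and with 10% it is 57–60%. The literal reading allows success with as few as 53.3% of those enrolled engaged. That figure is an upper bound on the distortion, since it assumes that all attrition precedes week 24 and that nobody lost was engaged. None of these figures is a prediction, because the document gives neither the never-starter share nor the timing of attrition.

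**What to change.** - Confine the all-randomised definition in {20c} to Step 2 analyses.
- Define the primary set as every participant confirmed eligible and enrolled into Step 1.
- Count as non-engaged both those who never start and those who stop before completing the planned intervention, with one trigger worded identically in {20a} and {20c}.
- Report the proportion among starters as a sensitivity analysis.

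No new data are needed, since device logs show zero use, and the sample size and stated power stand (98.3% at n = 225). The headline engagement rate may come out slightly lower.

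Timing needs care. Trial status reports that recruitment ended in August 2024, and Data management {19} plans a lock after the 3-month visits. The clarification should be dated and should state whether Step 1 engagement data had been seen. If they had, the proportions on both denominators should be reported side by side.
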